### **Surgery**

Caution is advised on theoretical grounds for any surgical procedures during the study. The appropriate interval of time between surgery and evorpaccept (ALX148) required to minimize the risk of impaired wound healing and bleeding has not been determined. Stopping evorpaccept (ALX148) is recommended at least 7 days prior to surgery. Postoperatively, the decision to reinstitute evorpaccept (ALX148) treatment should be based on a clinical assessment of

satisfactory wound healing and recovery from surgery. The Investigator should refer to the US or local Package inserts for instructions on stopping/re-initiation of cetuximab and pembrolizumab.

## 6.6 CONCOMITANT THERAPY

All concomitant medications taken during study participation will be recorded continuously on the electronic case report forms (eCRFs), starting at the screening visit and ending 30 days from treatment discontinuation. For this protocol, a prescription medication is defined as a medication that can be prescribed only by a properly authorized/licensed clinician. Medications reported in the eCRF are concomitant prescription medications, over-the-counter medications, and non-prescription medications. Concomitant treatment considered necessary for the patient's well-being may be given at the discretion of the treating physician.

Examples of permitted concomitant therapies include but are not limited to:

- Oral contraceptives.
- Hormone-replacement therapy.
- Prophylactic or therapeutic anticoagulation therapy (such as low-molecular weight heparin or warfarin at a stable dose level).
- Inactive influenza vaccinations during influenza season.
- Megestrol administered as an appetite stimulant.
- Inhaled corticosteroids for chronic obstructive pulmonary disease.
- Mineralocorticoids (e.g., fludrocortisone).

### Radiation

Palliative radiotherapy on study is permitted for the treatment of painful bony lesions providing the lesions were known at the time of study entry and the Investigator clearly indicates that the need for palliative radiotherapy is not indicative of disease progression. Study treatment should be interrupted during palliative radiotherapy—stopping 7 days before and resuming treatment 7 days after. Irradiated lesions will be considered not evaluable for response but still can be used to assess disease progression. The intensities, number, and dates of doses received for allowed palliative radiotherapy should be recorded on the appropriate eCRFs.

#### 6.6.1 RESCUE MEDICINE

Anti-emetics and anti-diarrheal medications should not be administered prophylactically before initial treatment with study drugs. At the discretion of the investigator, prophylactic anti-emetic and anti-diarrheal medication(s) may be used per standard clinical practice before subsequent doses of study drugs.

Hematopoietic growth factors should not be administered prophylactically before initial treatment with study drugs. Hematopoietic growth factors and transfusions may be administered according to local guidelines if indicated during the study.

In general, investigators should manage a patient's care with supportive therapies as clinically indicated, as per local standards. Patients who experience infusion-associated symptoms may be treated symptomatically with acetaminophen, ibuprofen, diphenhydramine, and/or famotidine or another H2 receptor antagonist as per standard practice. Serious infusion-associated events manifested by dyspnea, hypotension, wheezing, bronchospasm, tachycardia, reduced oxygen saturation, or respiratory distress should be managed with supportive therapies as clinically indicated (e.g., supplemental oxygen and  $\beta_2$ -adrenergic agonists).

Guidelines for known toxicities of study agents are provided in the Appendix 1. All medications must be recorded on the Concomitant Medications eCRF.

## 7 STUDY INTERVENTION DISCONTINUATION AND PARTICIPANT DISCONTINUATION/WITHDRAWAL

### 7.1 DISCONTINUATION OF STUDY INTERVENTION (STOPPING RULES)

AGICC has the right to terminate the study intervention at any time. Reasons for terminating the study intervention may include, but are not limited to, the following:

- The incidence or severity of adverse events in this or other studies indicates a potential health hazard to patients
- Patient enrollment is unsatisfactory
- Poor protocol adherence
- Inaccurate or incomplete data recording
- Non-compliance with the International Conference on Harmonization (ICH) guideline for Good Clinical Practice
- No study activity (i.e., all patients have completed the study and all obligations have been fulfilled)

AGICC will notify ALX Oncology Ltd, Merck & Co, Inc., & Eli Lilly USA, LLC if they decide to discontinue the study intervention.

Discontinuation from study intervention does not mean discontinuation from the study, and remaining study procedures should be completed as indicated by the study protocol and Schedule of Events (Section 1.3). If a clinically significant finding is identified (including, but not limited to changes from baseline) after enrollment, the investigator or qualified designee will determine

if any change in subject management is needed. Any new clinically relevant finding will be reported as an adverse event (AE).

## 7.2 PARTICIPANT DISCONTINUATION/WITHDRAWAL FROM STUDY

Participants are free to withdraw from participation in the study at any time upon request.

In addition, the investigator has the right to withdraw a patient from the study at any time. Reasons for withdrawal from the study may include, but are not limited to, the following:

- Patient withdrawal of consent at any time
- Any medical condition that AGICC or the medical monitor determines may jeopardize the patient's safety if he or she continues in the study
- AGICC or the medical monitor determines it is in the best interest of the patient
- Patient non-compliance

Patients must discontinue study treatment if they experience any of the following:

- Disease progression (Patients are allowed to receive study treatment beyond RECIST v1.1-defined-disease progression if certain conditions are met (see Section 4.1.2)).
- Symptomatic deterioration attributed to disease progression as determined by the investigator after integrated assessment of radiographic data, biopsy results, and clinical status
- Intolerable toxicity related to any study drug (see section 12.1 for additional guidance)
- Any medical condition that may jeopardize the patient's safety if he or she continues study treatment
- Use of another non-protocol anti-cancer therapy
- Pregnancy

Every effort should be made to obtain information on patients who withdraw from the study. The primary reason for withdrawal from the study or study drug discontinuation should be documented on the appropriate eCRF. However, patients will not be followed for any reason after consent has been withdrawn. Patients enrolled in Stage 1 (safety run-in) who withdraw consent before completing the first cycle for reasons other than adverse events will be replaced. Patients who withdraw from Stage 2 of the study will not be replaced.

## 7.3 LOST TO FOLLOW-UP

A subject will be considered lost to follow-up if he or she fails to return for 3 scheduled visits and is unable to be contacted by the study staff.

The following actions must be taken if a subject fails to return to the clinic for a required study visit:

- Site will attempt to contact the subject and reschedule the missed visit and advise subject on importance of maintaining assigned visit schedule
- Before a subject is deemed lost to follow-up, the investigator will make every effort to regain contact with the subject. These contact attempts should be documented in the subject's medical record or study file
- Should the subject continue to be unreachable, he or she will be considered to have withdrawn from the study

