#### **8.2.5 AFTER TREATMENT / SURVIVAL FOLLOW-UP**

Overall survival information will be collected via telephone calls and/or clinic visits every 3 months  $\pm$ 14 days (first call and/or clinic visit to occur 3 months following the Final Study/Treatment Discontinuation Visit) until death, withdrawal of consent, the patient is lost to follow-up, study termination by AGICC, or a maximum of 2 years from the Final Study/Treatment Discontinuation Visit.

---

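### Survival collection stops at loss to follow-up, and Section 7.3 files unreachable patients as withdrawn although they have not withdrawn consent, so deaths can be missed

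*Protocol*

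**What the plan says.** Section 7.3 defines a lost patient as one who "fails to return for 3 scheduled visits and is unable to be contacted by the study staff". It asks for documented effort first: "Before a subject is deemed lost to follow-up, the investigator will make every effort to regain contact with the subject". It then closes the matter: "Should the subject continue to be unreachable, he or she will be considered to have withdrawn from the study".

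Section 8.2.5 collects OS by telephone and/or clinic visit at 3-monthly intervals. It sets these end points: "until death, withdrawal of consent, the patient is lost to follow-up, study termination by AGICC, or a maximum of 2 years". The 2-year limit is counted from the visit that closes treatment. The same list of end points stands in Section 1.3 (footnote 25), Section 4.1.2 and Section 4.4. Withdrawal of consent and loss to follow-up are separate items in it.

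Section 7.2 says two things about patients who leave. The first is a duty: "Every effort should be made to obtain information on patients who withdraw from the study". The second is a limit: "However, patients will not be followed for any reason after consent has been withdrawn".

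Section 8.3.5 asks that deaths from any cause after the adverse event reporting period be reported on the long-term survival form. Section 9.1 lists improved OS against historical controls as a secondary hypothesis. Section 9.4.3 says that OS has no power calculation and will be compared with historical controls if sample size allows.

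**The concern.** A patient with refractory metastatic colorectal cancer who stops attending and cannot be reached may have deteriorated or died. Under Section 8.2.5 the named route for learning of the death closes when that patient is classed as lost. Section 7.3 then puts the patient in the same category as those who chose to leave, although consent stands and vital status could still be sought.

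The sections leave a site unsure what to do. Section 8.2.5 says to stop, Section 7.2 says to make every effort for patients who withdraw from the study, and Section 8.3.5 says to report every death. No section names medical records, treating clinicians or public death records as a source of vital status.

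What is at stake is a possible upward bias in OS, in the direction of the stated hypothesis and with no concurrent control arm to share it. An analysis plan can set a censoring rule, but it cannot recover a date of death that sites were told to stop seeking.

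**Working it through.** The protocol gives no OS event count, benchmark, power or loss rate, so there is no OS figure to reproduce. The check has three parts.

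**1. Which sentence ends survival collection?** Set side by side:
- Section 8.2.5 and its three matching passages stop at loss to follow-up, listed separately from withdrawal of consent. This alone ends contact.
- Section 7.3 adds the label of withdrawn from the study. Deleting that sentence alone would leave the Section 8.2.5 stop in place.
- The Section 7.2 limit applies once consent is withdrawn. An unreachable patient has not done that, so the limit does not literally apply, while the duty to seek information does.

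The operative rule is therefore in Section 8.2.5. Section 7.3 blurs the distinction that would allow tracing to continue.

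**2. How quickly can the status apply?** During weekly treatment, the third missed visit falls 3 × 7 = 21 days after the last one attended, and contact must also have failed. In survival follow-up, contacts are 3 months apart, so three missed contacts span about 3 × 3 = 9 months.

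With an assumed exponential survival time and a 7-month median, the share of patients alive at one 3-monthly contact who die before the next is 1 − 2^(−3/7) = 0.26. Death is thus a plausible reason for not answering.

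**3. How large could the effect be?** Inputs from the protocol:
- N = 48 (Section 5.5).
- Median OS in Appendix 4: 6.4 to 8.8 months in the regorafenib and trifluridine-tipiracil arms. The lowest value for pembrolizumab in microsatellite stable disease, and for placebo in the first regorafenib trial, is 5.0. True medians of 5.0, 7.0 and 8.8 months were used.

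Assumptions:
- Exponential survival and administrative censoring at 24 to 36 months.
- 4 or 8 patients lost. These are illustrative counts, since no loss rate is stated.
- Two patterns. Either loss is unrelated to death, or each lost patient who dies within follow-up is censored 0 to 3 months before an unreported death. The 3 months match the contact interval in Section 8.2.5.

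Mean Kaplan-Meier median (months) over 4,000 simulated trials per cell:

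| True median | Lost | Loss unrelated to death | Lost shortly before an unreported death |
|---|---|---|---|
| 5.0 | 0 | 4.91 | 4.92 |
| 5.0 | 4 | 5.06 | 5.44 |
| 5.0 | 8 | 5.09 | 5.91 |
| 7.0 | 0 | 6.93 | 6.87 |
| 7.0 | 4 | 7.04 | 7.68 |
| 7.0 | 8 | 7.10 | 8.36 |
| 8.8 | 0 | 8.65 | 8.65 |
| 8.8 | 4 | 8.86 | 9.67 |
| 8.8 | 8 | 8.94 | 10.44 |

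The two columns were simulated separately, so their zero-loss rows differ slightly by chance.

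- Death-related loss of 4: 5.44 − 4.92 = 0.52, 7.68 − 6.87 = 0.81 and 9.67 − 8.65 = 1.02 months, or 11% to 12%.
- Death-related loss of 8: 0.99, 1.49 and 1.79 months, or 20% to 22%.
- Loss of 4 unrelated to death, at a true median of 7.0: 7.04 − 6.93 = 0.11 month. The median implied by the event rate hardly moves (6.89 with none lost, 6.84 with 4).

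A rough cross-check: if 4 of 48 deaths go unrecorded and follow-up time is kept, an exponential median of 7 becomes 7 / (1 − 4/48) = 7.6. With 8 it becomes 7 / (1 − 8/48) = 8.4.

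For scale, the active-minus-placebo differences in median OS for the four third-line trials in Appendix 4 are 6.4 − 5.0 = 1.4, 8.8 − 6.3 = 2.5, 7.1 − 5.3 = 1.8 and 7.8 − 7.1 = 0.7 months.

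**The case against.** The strongest reply is that the protocol already protects OS reasonably well. Section 7.3 requires documented effort before anyone is classed as lost, Section 7.2 requires effort to obtain information on patients who leave, Section 8.3.5 asks for all deaths, and nothing forbids looking in medical records. The status needs failed contact as well as missed visits, and in survival follow-up it would take many months to reach. The protocol states no OS censoring rule, but that commonly sits in the analysis plan and is no fault here. OS is unpowered and only conditionally compared.

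Most of this stands, and it limits the point. It does not remove it: general duties to make an effort and to report deaths name no source for the information, and Section 8.2.5 still tells sites that collection ends at loss to follow-up.

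Three stronger readings are tempting, and the documents support none of them:
- A reader might infer that the Section 7.3 label itself cuts off survival data through the Section 7.2 limit. It does not. That limit concerns withdrawn consent, and the stop comes from Section 8.2.5.
- A reader might infer that OS is overstated against historical controls. That requires loss related to death and less such loss in the historical trials. The protocol shows neither.
- A reader might take the 4 non-completers in Section 5.5 as an expected loss within the 48. They are a recruitment allowance on top of it (48 + 4 + 4 = 56), and nothing describes them as unreachable. The count of 4 used here is only an illustration.

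**Conclusion.** The point holds as a weakness in the stated follow-up rules, not as a demonstrated bias. Section 8.2.5 and its matching passages end vital-status collection for patients who have not withdrawn consent, Section 7.3 blurs their status, and both sit poorly with Sections 7.2 and 8.3.5.

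If loss is related to death, OS can be overstated. Four such losses among 48 would raise the Kaplan-Meier median by about 0.8 month at a true median of 7 months, and by 0.5 to 1.0 month across true medians of 5.0 to 8.8. This rests on exponential survival, on an assumed number of losses, and on every lost patient who dies doing so, unreported, within 3 months of last contact. Loss unrelated to death gives almost no bias.

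The priority is modest. OS is an unpowered secondary endpoint, and the primary response-rate test and the futility rule are untouched. The change is worth making because it is cheap.

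**What to change.** - **Section 7.3:** remove the reclassification as withdrawn, and keep loss to follow-up as a status of its own, distinct from withdrawal of consent.
- **Section 8.2.5, with Section 1.3 (footnote 25), 4.1.2 and 4.4:** remove loss to follow-up as an end to vital-status ascertainment. For every patient who has not withdrawn consent, allow the date of death, or the date last known alive, to be taken from medical records, treating clinicians or public death records, up to the existing 2-year limit.
- **Reporting:** give the number of patients whose OS is censored because contact was lost.

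All four survival passages need the edit, because changing Section 7.3 alone would leave the stop in place. The cost is a protocol and consent wording change and a small records check before the OS analysis. No visits or patients are added.

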## 8 STUDY ASSESSMENTS AND PROCEDURES

Please see Section 1.3 (Schedule of Events) for the schedule of events to be performed in this study.

### 8.1 EFFICACY ASSESSMENTS

Baseline tumor assessments should be performed  $\leq 28$  days before Cycle 1 Day 1 and assessed according to RECIST v1.1 and iRECIST (see Appendix 2). The same procedure used to assess disease sites at baseline should be used throughout the study (e.g., the same contrast protocol for CT scans or MRI scans). CT or MRI scans should include chest, abdomen, and pelvic scans; and other areas as clinically indicated. At the investigator's discretion, imaging may be repeated at any time if progressive disease is suspected. Evaluation of tumor response conforming to RECIST v1.1 and iRECIST must be documented every 9 weeks  $\pm 5$  days (no matter where the patient is in the treatment cycle). Patients in both the safety run-in and dose expansion stages will continue to receive study therapy until disease progression according to RECIST v1.1 (Appendix 2), unacceptable toxicity, death, patient or physician decision to withdraw, or pregnancy, whichever occurs first.

In all cohorts, at the time of RECIST v1.1-defined progression (i.e. iUPD), treatment is permitted to continue until the next assessment (at least 4 weeks but no longer than 8 weeks later) if the following criteria are met:

- Patient is clinically stable (An assignment of clinical stability requires that no worsening of performance status has occurred, that no clinically relevant increases in disease-related symptoms such as pain or dyspnea occur that are thought to be associated with disease progression (these symptoms are generally understood to mean a requirement for increased palliative intervention), and that no requirement for intensified management of disease-related symptoms exists, including increased

- analgesia, radiotherapy, or other palliative care.)
- Absence of tumor progression at critical anatomical sites (e.g., leptomeningeal disease) that cannot be managed by protocol-allowed medical interventions
  - Patient and investigator agree to continue treatment
  - Patient signs the Treatment Beyond Progression Informed Consent Form
  - If the subsequent scan continues to show progression, all therapy will be discontinued and the patient will be taken off study.

If iUPD is noted, a follow-up scan should be obtained at least 4 weeks but no longer than 8 weeks later. Schedule of tumor assessments are independent of any changes to the study treatment administration schedule (e.g., dose delay) and may occur mid-cycle depending on length of cycle. If a tumor assessment must be performed early or late, subsequent assessments should be conducted according to the original schedule based on the date of first study drug administration (Cycle 1, Day 1). Confirmation of response (PR or complete response [CR]) will be done no earlier than 28 days from study entry. In the case of SD, measurements must have met the SD criteria at least once after study entry at a minimum interval not less than 6 weeks. Patients who discontinue study treatment for any reason other than disease progression will continue to undergo tumor response evaluations (approximately every 9 weeks) until progressive disease. Rising tumor markers (e.g., CEA) in the absence of radiological evidence of progression is not considered progressive disease.

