Using a Simon-like 2-stage design, ORR will be determined based on the first 24 evaluable patients (including patients in both Stage 1 and Stage 2). If there are no responses (partial response or complete response as defined in the protocol) in the first 24 evaluable patients, then study enrollment will be stopped for futility. If there is at least one response (partial response or complete response as defined in the protocol) in the first 24 evaluable patients then full study enrollment will proceed as planned. If there are no responses (partial response or complete response as defined in the protocol) in the first 23 evaluable patients then enrollment will be temporarily paused to allow response evaluation of the 24th evaluable patient after up to 15 total weeks (ie 5 total cycles) of study therapy. If the 24th patient has response (partial response or complete response as defined in the protocol) then then full study enrollment will proceed as planned. If the 24th patient does not have a response (partial response or complete response as defined in the protocol) then the study will be stopped for futility. See Section 9.4.2 for statistical considerations.

A subset of patients (Cohort A) will undergo paired pre- and post- (around C3D1) treatment biopsies. See Section 4.1.4 for additional information regarding tumor biopsies.

There will be a 4-week window during which screening can occur. Patients in both the safety run-in and dose expansion stages will continue to receive study therapy until disease progression according to RECIST v1.1 (Appendix 2), unacceptable toxicity, death, patient or physician decision to withdraw, or pregnancy, whichever occurs first. The maximum duration of pembrolizumab is 35 cycles. There is no maximum duration of evorpacept (ALX148) or cetuximab.

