## 8.2 SAFETY AND OTHER ASSESSMENTS

### 8.2.1 SCREENING

Screening is to be done within 28 days prior to study entry (i.e. prior to Cycle 1 Day 1 (C1D1)). Written informed consent must be obtained prior to undergoing study specific procedures.

The following assessments will be conducted to determine eligibility. All of these investigations must be completed, reviewed, and recorded as part of the screening process. The investigator will maintain a screening log to record details of all patients screened irrespective of eligibility. Site staff will collect the blood samples for these standard blood tests. Any pre-existing baseline abnormality must be graded and recorded as per NCI-CTCAE v5.0.

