## 12.2 APPENDIX 2: PROTOCOL CRITERIA FOR MEASUREMENT OF STUDY EFFICACY ENDPOINTS (RECIST V1.1 AND IRECIST)

### 1 Definitions

1.1 Evaluable for adverse events. All patients will be evaluable for adverse event evaluation from the time of their first treatment.

1.2 Evaluable for response. All patients who have received at least one cycle of therapy and have their disease re-evaluated will be considered evaluable for response (exceptions will be those who exhibit objective disease progression prior to the end of cycle 1 who will also be considered evaluable). Patients on therapy for at least this period and who meet the other listed criteria will have their response classified according to the definitions set out below.

Response and progression will be evaluated in this study using the revised international criteria (1.1) proposed by the RECIST (Response Evaluation Criteria in Solid Tumors) committee as well as the modified iRECIST guidelines. Investigators should note the different requirements for confirmatory scans as well as follow up for the two criteria.

See section 4.1.2 for criteria for continuing treatment past RECIST 1.1 disease progression.

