## 2.5 Response.

All patients will have their BEST RESPONSE from the start of study treatment until the end of treatment classified as outlined below:

Complete Response (CR): disappearance of target and non-target lesions and normalization of tumor markers. Pathological lymph nodes must have short axis measures <10 mm (Note: continue to record the measurement even if <10 mm and considered CR). Residual lesions (other than nodes <10 mm) thought to be non-malignant should be further investigated (by cytology specialized imaging or other techniques as appropriate for individual cases before CR can be accepted).

Partial Response (PR): at least a 30% decrease in the sum of measures (longest diameter for tumor lesions and short axis measure for nodes) of target lesions, taking as reference the baseline sum of diameters. Non target lesions must be non-PD.

Stable Disease (SD): Neither sufficient shrinkage to qualify for PR nor sufficient increase to qualify for PD taking as reference the smallest sum of diameters on study.

Progressive Disease (PD): at least a 20% increase in the sum of diameters of measured lesions taking as references the smallest sum of diameters recorded on study (including baseline) AND an absolute increase of  $\geq 5$  mm. Appearance of new lesions will also constitute progressive disease (including lesions in previously unassessed areas). In exceptional circumstances, unequivocal progression of non-target disease may be accepted as evidence of disease progression, where the overall tumor burden has increased sufficiently to merit discontinuation of treatment or where the tumor burden appears to have increased by at least 73% in volume. Modest increases in the size of one or more non-target lesions are NOT considered unequivocal progression. If the evidence of PD is equivocal (target or non-target), treatment may continue until the next assessment, but if confirmed, the earlier date must be used.

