**Table 6: iRECIST Best Overall Response (iBOR)**

| TPR1 | TPR2               | TPR3               | TPR4                     | TPR5                          | iBOR |
|------|--------------------|--------------------|--------------------------|-------------------------------|------|
| iCR  | iCR, iPR, iUPD, NE | iCR, iPR, iUPD, NE | iUPD                     | iCPD                          | iCR  |
| iUPD | iPR, iSD, NE       | iCR                | iCR, iPR, iSD, iUPD, NE  | iCR, iPR, iSD, iUPD, iCPD, NE | iCR  |
| iUPD | iPR                | iPR, iSD, iUPD, NE | iPR, iSD, iUPD, NE, iCPD | iPR, iSD, iUPD, NE, iCPD      | iPR  |
| iUPD | iSD, NE            | PR                 | iPR, iSD, iUPD, NE       | iPR, iSD, iUPD, iCPD, NE      | iPR  |
| iUPD | iSD                | iSD, iUPD, NE      | iSD, iUPD, iCPD, NE      | iSD, iUPD, iCPD, NE           | iSD  |
| iUPD | iCPD               | Anything           | Anything                 | Anything                      | iCPD |
| iUPD | iUPD               | iCPD               | Anything                 | Anything                      | iCPD |
| iUPD | NE                 | NE                 | NE                       | NE                            | iUPD |

- Table assumes a randomised study where confirmation of CR or PR is not required.
- NE = not evaluable that cycle.
- Designation “I” for BOR can be used to indicate prior iUPD to aid in data interpretation.
- For patients with non-target disease only at baseline, only CR or non-CR/non-PD can be assigned at each TPR but is not shown in the table for ease of presentation.

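### The response-confirmation rule is timed from study entry instead of from the first response, so it permits a PR or CR seen on one scan to count in the primary ORR and the 0/24 futility rule

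*Protocol*

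**What the plan says.** Protocol section 8.1 and Table 1 footnote 20 carry the same sentence: "Confirmation of response (PR or complete response [CR]) will be done no earlier than 28 days from study entry". Section 8.2.1 fixes what study entry means: "Screening is to be done within 28 days prior to study entry (i.e. prior to Cycle 1 Day 1 (C1D1"). Section 8.1 also sets the imaging schedule: "Evaluation of tumor response conforming to RECIST v1.1 and iRECIST must be documented every 9 weeks", with a window of ± 5 days.

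Appendix 2 (section 12.2) defines the response categories. In its item 2.5, PR is "at least a 30% decrease in the sum of measures" of the target lesions relative to baseline. Neither the PR nor the CR definition asks for a repeat scan, and neither do the PR and CR rows of Table 4. Item 1 of the appendix says "Investigators should note the different requirements for confirmatory scans as well as follow up for the two criteria", but the appendix then sets out only how progression is confirmed under iRECIST. The one explicit remark on confirming responses is a note to Table 6, the iRECIST best-response table: "Table assumes a randomised study where confirmation of CR or PR is not required".

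ORR per RECIST v1.1 is a primary endpoint (section 3). Section 9.4.2 tests it one-sided at 0.05 against 3%, with 48 patients and a stated 87% power at 15%. Enrollment stops if none of the first 24 evaluable patients responds. For the last of these, section 4.1.1 says "enrollment will be temporarily paused to allow response evaluation of the 24th evaluable patient after up to 15 total weeks".

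**The concern.** A confirmation rule exists to check an earlier observation. This one does not refer to an earlier observation: its clock starts at the first dose. On the scheduled scans, the scan that first shows a PR already satisfies it. Nothing elsewhere in the protocol supplies an interval, and the endpoint is not labelled confirmed or unconfirmed. Two readers could count different responders from the same images.

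The trial has no control arm in which measurement error or short-lived shrinkage would appear equally. Any single-scan response that later vanishes adds directly to the numerator tested against a fixed 3%. The futility rule is more exposed still, because one such response among 24 patients keeps the trial open.

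**Working it through.** **Timing.** Scans are at 9 weeks ± 5 days.
- First scheduled scan: 63 ± 5 = day 58 to 68, always later than day 28.
- Second scheduled scan: 126 ± 5 = day 121 to 131.
- Evaluation limit for the 24th patient: 15 × 7 = day 105.

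Only one scheduled scan falls inside the 24th patient's window. A PR first seen on day 58 to 68 could be re-scanned 28 days later (day 86 to 96) within the window, but only by a scan that is not on the schedule.

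**The plan's own figure.** The protocol states no cut-off, so I derived it from P(X ≥ r) = 1 − Σ C(48,x) pˣ(1−p)^(48−x), with the sum over x = 0 to r−1.
- r = 4: P at 3% is 0.0555, above 0.05.
- r = 5: P at 3% is 0.0143; at 15% it is 0.866, which matches the stated 87%.

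The rule is therefore 5 or more responders of 48. Adding the 0/24 stop changes these to 0.0140 and 0.860, so the single-stage figures serve below.

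**Effect on type I error.** Let u be the share of first responses that would not confirm. The protocol gives no value, so 0 to 50% is my assumed range. Suppose also that the 3% null is a confirmed rate. The single-scan rate under the null is then 0.03/(1−u).

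| u (assumed) | single-scan rate | P(≥5 of 48) | P(0 of 24) |
|---|---|---|---|
| 0 | 3.0% | 0.014 | 0.48 |
| 10% | 3.33% | 0.021 | 0.44 |
| 20% | 3.75% | 0.033 | 0.40 |
| 30% | 4.29% | 0.054 | 0.35 |
| one third | 4.5% | 0.064 | 0.33 |
| 50% | 6.0% | 0.159 | 0.23 |

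The last column is (1−p)²⁴. Type I error reaches 0.05 at a single-scan rate of about 4.2%, that is at u = 1 − 0.03/0.042, or about 29%.

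**Effect on power if confirmation is required.** If the 15% target was meant as a single-scan rate, the confirmed rate is 0.15(1−u). Power at 5 or more of 48 is then:
- u = 0: 15%, power 87%.
- u = 20%: 12%, power 70%.
- u = one third: 10%, power 53%.
- u = 50%: 7.5%, power 29%.

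**The case against.** The text says that confirmation will be done. It does not say that a first scan confirms itself. A reader might infer that every responder counts on one scan and that ORR is inflated. The protocol supports neither as fact: single-scan counting is a reading that the wording permits, and inflation is a risk. Section 8.1 also allows extra imaging when progression is suspected, so the 28-day limit could bind on an early unscheduled scan.

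The note to Table 6 might be taken as a declaration that responses need no confirmation. It belongs to the iRECIST table, which serves exploratory endpoints, and does not govern the RECIST v1.1 primary endpoint.

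The numerical case can also be challenged. The protocol does not say whether the historical rates behind 3% were confirmed; if they were not, single-scan counting compares like with like. Appendix 4 lists third-line ORRs of 1.0, 4.9, 1.6 and 1.1%, so 3% is above three of the four. Divided by two thirds, those three become 1.5, 2.4 and 1.65%, still below 3%. The attained level of 0.014 leaves further room.

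These points stand, and they make the size conditional. They do not repair the rule, which still gives no interval from first response and leaves the primary endpoint open to two counts.

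On the best-response window, item 2.5 of Appendix 2 reads "All patients will have their BEST RESPONSE from the start of study treatment until the end of treatment classified as outlined below", and section 4.1.2 allows treatment past RECIST progression. A reader might infer that a PR after RECIST PD becomes a RECIST response and that the RECIST versus iRECIST comparison is lost. Appendix 2 section 3 records iRECIST responses separately and treats a response after unconfirmed progression as an iRECIST feature, so that inference goes too far. What remains is that the window is not closed at RECIST PD. It also conflicts with section 8.1, which keeps scanning patients who stop for other reasons.

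**Conclusion.** The point holds as a defect in a stated rule. Confirmation is anchored to Cycle 1 Day 1, the limit is met by every scheduled scan, and the response definitions ask for no repeat. Single-scan responses may therefore count in the primary ORR and in the 0/24 rule, with a possible upward bias.

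The bias cannot be sized from the protocol. Type I error stays below 0.05 until about 29% of first responses fail to confirm, and is 0.064 at one third and 0.16 at one half. The chance of stopping at 0/24 under the null falls from 0.48 to 0.33 and 0.23 at those two shares. All of this assumes that 3% is a confirmed rate and that the cut-off is 5 of 48.

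**What to change.** 1. Replace the sentence in section 8.1 and Table 1 footnote 20 with: *A PR or CR counts toward ORR only if the criteria are met again on a scan at least 28 days after they were first met.* Align Appendix 2, item 2.5 and Table 4.
2. Apply it to the final test and to the 24-patient look. Extend the 24th patient's window beyond 15 weeks so that any first PR or CR seen within it can have a confirmatory scan at least 28 days later. Moving the limit to a fixed week-18 date would not be enough, because a response first seen at week 18 could not be confirmed by then.
3. State that the 3% null and the 15% target are both confirmed rates. Then 48 patients and the cut-off of 5 can stay. Otherwise restate the power, for example 53% if the confirmed rate is 10%.
4. Separately, close the RECIST v1.1 best-response window at first RECIST PD or new anticancer therapy instead of at the end of treatment. Responses after RECIST PD are then credited only under iRECIST, and responses on continued scans after stopping for reasons other than progression are counted.

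The cost is protocol wording, a longer futility pause and possibly a lower reported ORR. The next 9-weekly scan can usually confirm: week 18 comes 53 (121 − 68) to 73 (131 − 58) days after a first response at week 9. Waiting for it takes the 24th patient to day 131 at the latest, 26 days past the present limit.
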